**Data collection and quality control**

The study tools will be initially prepared in English, translated to Sidamic language, and reconverted back to English to retain its originality and consistency. The assessment will be conducted to evaluate the inconsistency among the 2 versions of the tools. It will be pre-tested on the 5% of sample size in kebeles that are not involved in the actual research area. Then, any inconsistency between the 2 versions will be amended accordingly. The training regarding tools will be provided for the data collectors and supervisors by the principal investigator for two days. During the training, attention will be given to the significance of the study, data collection procedure, objective, methods, and ethical issues. The quantitative and qualitative data collection will be conducted by employees of Hawassa University Health and Demographic Surveillance System (HDSS) and masters of public health experts. Two public health experts with RH will be carefully supervised the data collection method. The consistent checkup for incompleteness and non-consistency of the data will be made on a daily basis. Double data entry will be carried out. The incomplete, inconsistent, and invalid data will be distinguished correctly to acquire a high quality of data before, during, and after data entry. The corrections will be made based on the original data.

**Intervention procedure**

WDA volunteers will be recruited by using the following selection criteria as able to read and write the Sidama language and are willing to do the intervention. Following recruitment, intensive training will be given for 1 week on the topics. One health education session consists of key messages on normal pregnancy, danger signs and complications during pregnancy, delivery, and the postpartum period, the practice of birth preparedness as well as complication readiness, and the benefits of MHSU. The other actions executed by WDA facilitators will be the motivating mother and their families for MHSU. One hour will be allocated for each session, from this 20 minutes will be allowed for the lecture which is moralistic in nature and the remaining 40 minutes will be allowed for raising questions and responses. After the session, some of the women will be selected to carry out role play which is basic to demonstrate the important messages and share experiences. This will be done to repeat the information provided to enable them to internalize the key message. The women will be also exposed to posters to reinforce the session message. The session will be conducted 2 times per month for six months. The follow-up will be conducted every month or more repeatedly if any potential problems indicated.

Interventional group (n= 563)

Control group (n= 563)

Included in to study (n = 1,126)

Randomization

Received CLHEI (n= 563)

Loss to follow up (n=)

Loss to follow-up (n=)

Analyzed at 6 months (n=)

Received routine intervention (n= 563)

Analyzed at 6 months (n=)

**Figure 1:** Flow Diagram for randomization of study participants in to intervention and control groups in Dale and Wonsho districts of Sidama region, Ethiopia.

**The study variables**

| Outcome variables | Definition |
| --- | --- |
| MHSU | Utilization of maternal health care measured using the yes or no questions at the baseline and after 6 months of intervention. |
| Knowledge of obstetrics danger signs | Will be measured by using the 30 knowledge assessment questions. |
| Birth preparedness and complication readiness practice | Will be assessed using the 5 practice assessment questions. |
| Perceptions, barriers, and facilitators | Perceptions, barriers, and facilitators of MHSU that affect the utilization of MHS will be explored qualitatively. |
| Exposure variable | Definition |
| Health education | **Intervention group:** will receive routine plus pre-recorded audio-based HEI package for six months until date of delivery.  **Comparator group:** will receive the routine health education package for six months until the date of delivery as per the Ethiopian guidelines. |
| Predictors | Predictors that predict the utilization of MHS. It will be measured retrospectively. Socio-economic and demographic, obstetric characteristics, health facility and socio-cultural related predictors. |
| Covariates | Place of residence (urban/rural), educational status of women and her spouse, wealth index, maternal age, occupational status of women and her spouse |

**Data source**

The data sources are women of reproductive age, service users and providers.

**The measurements**

**ANC utilization** is measured as a proportion of women who utilized ANC from skilled providers (HEWs, midwives, nurses, health officers, and doctors) at least once during the last pregnancy using a woman's self-report. However, different studies considered different figures of ANC visits being optimum. For instance, some researchers had fixed 2 ANC visits to be adequate. The WHO suggests at least 8 ANC visits throughout pregnancy while the first visit will be conducted before 16 weeks or within the first trimester. Therefore, standardization of the numbers of ANC use is required to assist the comparison of diverse or different studies. Accordingly, we considered utilization of ANC as a woman who has at least one ANC follow-up which is similar to EDHS. Besides, the time must be within the first trimester or before 16 weeks of gestation. Moreover, women must consume more than 90 iron-folic acids (IFA) tablets or syrup, receive at least one dose of tetanus toxoid injection, have a laboratory test result of syphilis, and blood group.

**Institutional delivery utilization** is measured as the proportion of women who utilized institutions (governmental health centers or hospitals, and/or private hospitals or clinics) for delivery in their last pregnancy using a woman’s self-report.

**PNC utilization** is measured as the proportion of women who utilized a PNC visit within 42 days after giving birth at least once using a woman’s self-report.

**Maternal knowledge regarding ODS** will be measured using the 30 questions during three phases namely antepartum (9 questions), intrapartum (12 questions), and postpartum (9 questions). The correct answers are assigned a score of 1, while incorrect answers are assigned a score of 0. Lastly, the total knowledge scores range from 0 to 30. The study respondents who spontaneously mention at least 3 ODS during each phase are classified as having “good knowledge” and those who are not able to spontaneously mention 2 or fewer ODS have “poor knowledge”.

**Spontaneous knowledge** is defined as the knowledge of study participants who can name or call an ODS without being read the name of that sign by data collectors. Merely true ODS spontaneously mentioned by study participants will be recorded during the interview.

**BPCR practice** will be measured using 5 components of the question as to whether or not the woman planned for her most recent pregnancy such as identified a closer proper HF for childbirth, founded and communicate an SBA, saved money, a material resource for childbirth, and other associated costs, prepared or arranged transportation to a proper HF in case of childbirth and obstetric emergency and identified and fixed the compatible blood group givers in case of blood requirements. If a woman prearranged at least three components out of 5, she will be considered as having “well prepared” and those who are prepared 2 or fewer considered “poorly prepared”.

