**Study subject**

Study subject will be all WRA, service users and providers, all pregnant women residing in Dale and Wonsho districts of the Sidama region, Ethiopia.

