**The inclusion and exclusion criteria**

All systematically selected WRA who gave live birth in the last 12 months, all purposely selected service providers and users, all pregnant mothers residing in the selected *kebeles* for at least for 6 months and have no plan to change residence during the implementation of an intervention, no psychiatric problems, capable of providing written informed consent, and voluntary to be visited by WDT facilitators, data collectors, and supervisors will be included for this study. Women who have a severe illness during the data collection period will be excluded from this study due to unable to communicate. Also, study subject who have a psychiatric disorder will be excluded due to that could affect participation and consent procedure. Similarly, women who experienced stillbirth and infant deaths will be excluded because the questions from this study are expected to re-memorize women the unfavorable pregnancy outcome they had faced. This may seriously affect maternal participation and genuine response. Midwives who have been serving in the maternal and child health case team for less than two years will be excluded. Due to this reason, these midwives have less experience and interaction with pregnant women and couldn’t provide in-depth information on perceptions, barriers, and facilitators of MHSU. Moreover, all WRA included in the quantitative study will be excluded because they have information during the quantitative study that may introduce information bias.

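### The trial's ANC outcome requires a visit before 16 weeks, a condition that is closed or nearly closed when a woman is first exposed, so the ANC comparison is pulled towards no effect

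*Protocol*

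**What the plan says.** In the Protocol, The measurements, the ANC definition begins with a simple criterion: "we considered utilization of ANC as a woman who has at least one ANC follow-up which is similar to EDHS". It then adds conditions that read as cumulative. The first is timing: "Besides, the time must be within the first trimester or before 16 weeks of gestation". The next sentence adds that "women must consume more than 90 iron-folic acids (IFA) tablets or syrup, receive at least one dose of tetanus toxoid injection", together with a syphilis test result and a blood group. The wording is retrospective (self-report about the last pregnancy), and no other ANC definition is given for the trial.

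The trial population is described in Study subject as "all pregnant women residing in Dale and Wonsho districts of the Sidama region, Ethiopia" and in The inclusion and exclusion criteria as "all pregnant mothers residing in the selected *kebeles* for at least for 6 months", followed by conditions on residence, mental health and consent. No gestational age is mentioned.

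The study variables table says that the intervention group "will receive routine plus pre-recorded audio-based HEI package for six months until date of delivery", with a matching period for the comparator. Intervention procedure gives the frequency: "The session will be conducted 2 times per month for six months". Utilization is measured at baseline and after six months of intervention.

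**The concern.** The definition suits the cross-sectional survey (Paper I), where the pregnancy is over and every component can be scored looking back. In the trial the same women are followed forward from a baseline in pregnancy. Education given after week 16 cannot create a visit before week 16.

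Because the conditions are cumulative, a woman who passes 16 weeks without a visit is scored as a non-user of ANC even if the programme then leads her to attend regularly. Such women add failures to both arms and no difference between them. The estimated effect on ANC use shrinks for a reason unrelated to whether the education works, and a null ANC result would be hard to interpret.

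**Working it through.** **Plan's own figure.** Two sessions a month for six months gives 2 × 6 = 12, which matches the 12 rounds in the Summary. The trial size of 1,126 comes from the utilization objective, but no rates, effect or design effect are given for it. It cannot be reproduced, and no power figure for ANC can be derived from it.

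**Reading 1: six months ending at delivery (The study variables).** Assume a 40-week pregnancy and six months of about 26 weeks.
- Gestation at start: 40 - 26 = 14 weeks, already past a 13-week first trimester.
- Time left before week 16: 16 - 14 = 2 weeks.
- Session spacing: 26 / 12 = 2.17 weeks, so 2 / 2.17 = 0.92, about one session of the 12.
- If six months is counted as 24 weeks, the start is at 16 weeks and nothing is left.

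**Reading 2: no gestational limit (Study subject; The inclusion and exclusion criteria).** The Protocol gives no distribution of gestation at enrolment. Assume it is uniform from a to b weeks. The share already at or past 16 weeks is then (b - 16) / (b - a):

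| Assumed range (weeks) | Share at or past 16 weeks |
| --- | --- |
| 0 to 28 | 12/28 = 43% |
| 4 to 28 | 12/24 = 50% |
| 0 to 36 | 20/36 = 56% |
| 0 to 40 | 24/40 = 60% |
| 4 to 40 | 24/36 = 67% |
| 8 to 40 | 24/32 = 75% |

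Lower limits of 0 to 8 weeks with upper limits of 28 to 40 weeks thus give about 43% to 75%. A later lower limit raises the share (12 to 40 weeks: 24/28 = 86%).

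**From share to dilution.** Being past 16 weeks does not by itself shut a woman out. There are three cases:
- First exposed at 16 weeks or later, no early visit: fixed failure on the ANC outcome.
- Early visit already made: timing already met. The outcome can still move through the IFA, tetanus toxoid and laboratory items.
- First exposed before 16 weeks, no visit yet: all components open, but the time left for the visit may be short.

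Let L be the share at or past 16 weeks and e the proportion of those women with an early visit. If everyone not shut out responds equally (an assumption), the retained fraction of the effect is 1 - L(1 - e):

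| L | e = 0 | e = 0.25 | e = 0.50 |
| --- | --- | --- | --- |
| 0.43 | 57% | 68% | 79% |
| 0.60 | 40% | 55% | 70% |
| 0.75 | 25% | 44% | 63% |

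Neither L nor e is in the Protocol. The table shows how much the answer depends on them and is not an estimate.

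**The case against.** The strongest reply is that open enrolment is inferred from silence. Both arms are to receive their package for six months until delivery, and a woman enrolled late in pregnancy could not receive all 12 sessions before delivery. Read that way, everyone starts near 14 weeks and nobody is past 16 weeks at the start. This stands as far as it goes. A reader might infer that women join at any gestation and that timing is settled beforehand for most of them. The Protocol establishes neither: the first conflicts with the exposure period, and the second needs a gestation distribution that is not given. The reply does not rescue the outcome, because a 14-week start leaves only about two weeks.

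A reader might also infer that the ANC outcome cannot change at all after 16 weeks, and derive a large multiple of the sample size from that. This is not supported. It treats late enrollees who already had an early visit as unable to respond, when the other components remain open to them where enough of the pregnancy is left.

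Two further strong readings fail. The first-trimester and 16-week limits might look like conflicting cut-offs, but they are offered as alternatives and together reduce to before 16 weeks. Nor does the point reach maternal health service use as a whole: institutional delivery and PNC occur after enrolment, and randomisation is not undermined.

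**Conclusion.** The point holds for the ANC outcome of the trial. On either reading of the Protocol, the timing condition is closed or nearly closed at first exposure, and keeping it as a cumulative condition biases the ANC comparison towards no effect. The mechanism follows from the text alone, but its size does not. It depends on gestation at enrolment (43% to 75% at or past 16 weeks under the assumed uniform ranges) and on how many women already had an early visit, and the Protocol gives neither. The eligibility text, the exposure period and the ANC definition are also not consistent with one another on when in pregnancy a woman enters. Outcome definition and eligibility are both fixed in the Protocol, so this is not a detail left to an analysis plan.

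**What to change.** - For Paper IV, remove the before-16-weeks condition from the ANC outcome. Define ANC use by what can occur after enrolment, for example the remaining components, or ANC attendance between enrolment and delivery.
- Record gestation and number of prior ANC visits at baseline in both arms, and adjust the ANC comparison for them.
- Keep the composite with the timing condition for Paper I. In the trial it can be reported descriptively.
- Reconcile The inclusion and exclusion criteria, The study variables and The measurements on gestation at enrolment.

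An analysis restricted to women enrolled before 16 weeks with no prior visit is not needed. It could leave a small subgroup in an unmasked trial.

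The cost is a change of outcome wording and two baseline items. The downside is that the trial's ANC outcome will differ from the survey's, so the two papers' ANC figures will not be directly comparable.

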**Sample size calculation**

The adequate sample size for all objectives is calculated using openepi version 3 software. The sample size needed to estimate the utilization of MHS is calculated assuming the anticipated utilization of ANC (74%), births attended in an HF (48%), and PNC (34%) according to the report of 2019 Mini EDHS[[29](#_ENREF_29)], the margin of error of 5%, 95% confidence interval, 1.31 design effect. Based on the above information, the estimated sample size is 392 (ANC), 508 (births attended in a health facility), and 457 (PNC). The sample size needed for identifying the predictors associated with MHSU is calculated considering variables significantly associated with MHSU based on previous studies done in Northern Ethiopia [7], in rural Haramaya district, Eastern Ethiopia [10], and in Northwest Ethiopia [11]. For all calculations, power was set at 80%, level of confidence at 5%, and the ratio of unexposed-to-exposed were assumed to be 1. Hence, the sample size of 1,104 obtained from the second objective will be utilized due to it is the maximum sample size assessed and would be adequate to assess all objectives of this study. The minimum required sample size for the qualitative study will be determined according to the recommendation of Morse and Creswell for Phenomenological studies (20 in-depth interviews, 9 focus group discussions, and 20 key informant interviews) [[30](#_ENREF_30)]. The minimum required sample size for the third and fourth objectives is calculated based on the following considerations. Due to the lack of the previous cRCT on the same topic, assumptions on the proportion of women with knowledge on ODS in the control and intervention arms were taken from a previous quasi-experimental study. The proportion before the intervention was taken as the proportion in the control arm and the proportion after the intervention as the proportion in the intervention arm. Accordingly, P1 = 45.7% (proportion of women’s knowledge regarding ODS during pregnancy) in the control group, P2= 62.9% (proportion of women’s knowledge regarding ODS during pregnancy in the intervention arm) [[14](#_ENREF_14)], 95% CI, and 80% power. According to the above considerations, the estimated effective sample size for individual-based randomization is 286. For this objective, the sample size is adjusted to non-response rate (NRR) by dividing the initial sample size by the anticipated response rate. In case of knowledge regarding ODS during pregnancy, the adjusted sample size to NRR is 286/1 = 286.The minimum required number of clusters is computed by multiplying the effective sample size and ICC factors for both groups [28]. We received the typical value of ICC factor of 0.01 from range values (0.01 to 0.05) based on the existing recommendation [26]. Consequently, the minimum needed cluster number is 329*0.01 = 3.29 for both groups. Nevertheless, to maintain the sufficiency of the cluster and to have adequate power [26, 28], 12 clusters (*12 kebeles*) will be included in this study. To account for the effect of the cluster, the effective sample size is multiplied by a VIF of 1.26. The VIF is calculated with the assumption of an equal cluster size of 27 study subjects from 12 clusters (*kebeles*). Using ICC value of 0.01, (VIF = 1+ [(n-1) ICC]), where ‘n’ is the average cluster size [28]. Thus, the final estimated sample size is 360 (180 in the intervention arm and 180 in the control arm). However, the sample size calculated for the fourth objective which is designed to evaluate the effect of the intervention on MHSU is 1,126 (i.e., larger). Hence, the sample size of 1,126 obtained from the fourth objective will be utilized for this objective as well as it would be maximum or representatives of the sample for both objectives.

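### The protocol scores antenatal care use by two incompatible rules: at least one skilled-provider visit, and an all-or-nothing set of timing and content conditions

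*Protocol*

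**What the plan says.** Protocol, The measurements, opens the ANC paragraph with a contact measure. Use is "measured as a proportion of women who utilized ANC from skilled providers", at least once in the last pregnancy, by self-report. The paragraph notes that studies count different numbers of visits, argues that "standardization of the numbers of ANC use is required to assist the comparison of diverse or different studies", and states its choice: "we considered utilization of ANC as a woman who has at least one ANC follow-up which is similar to EDHS".

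The next two sentences add conditions, both worded as obligations:

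- Timing: "the time must be within the first trimester or before 16 weeks of gestation".
- Content: "Moreover, women must consume more than 90 iron-folic acids (IFA) tablets or syrup, receive at least one dose of tetanus toxoid injection", and further that women "have a laboratory test result of syphilis, and blood group".

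Nothing labels these conditions as separate quality indicators, and no scoring rule says how they combine with the visit. The outcome table (The study variables) says only "Utilization of maternal health care measured using the yes or no questions at the baseline and after 6 months of intervention". The Sample size calculation section plans on 74% ANC use, taken from the 2019 Mini EDHS. The other two services defined under The measurements, institutional delivery and postnatal care, are contact measures with no content conditions.

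**The concern.** The same paragraph classifies the same woman in two ways. A woman with one visit at 20 weeks is a user by the opening sentence and a non-user by the timing sentence. So is a woman seen early who took 60 tablets, or one with no syphilis result. The all-or-nothing rule is also not the EDHS-like measure that the paragraph says it adopts.

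ANC use is one of the three services whose use is evaluated in Paper I (prevalence and predictors) and Paper IV (effect of the education). Under Statistical data analysis, variables are recoded and categorized before the main analysis, and the Blinding section says nobody can be masked. With both rules in the protocol, an analyst who knows the allocation could choose between them after seeing the data. The choice changes the set of successes and can change the estimated effect.

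**Working it through.** **1. What the planning figure describes.** Inputs from Sample size calculation: p = 0.74, margin 0.05, 95% confidence, design effect 1.31.

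n = 1.31 × 1.96² × 0.74 × 0.26 / 0.05² = 1.31 × 295.65 = 387.3, against 392 stated (about 1.2% apart).

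The stated figure therefore rests on the EDHS-sourced 74%. The protocol does not label the 74% as at least one visit. That is an inference from the EDHS sentence under The measurements and from the separate 43% for four or more visits in the Introduction.

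**2. Whether one reading satisfies every sentence.**

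| Woman | Visit rule | All conditions |
|---|---|---|
| Early visit, all items met | user | user |
| First visit at 20 weeks, all items met | user | non-user |
| Early visit, 60 tablets, other items met | user | non-user |
| Early visit, no syphilis result | user | non-user |

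The rules agree only for women who meet everything and for women with no visit. The all-or-nothing rule also has gaps of its own: the iron-folic acid condition sets no amount for syrup, and the timing condition joins two limits with *or*.

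**3. How far apart the rules could be.** The protocol gives no prevalence for any item. Assumption: each of the four content items (iron-folic acid, tetanus, syphilis result, blood group) is met by a share c of attenders, with c between 0.5 and 0.8.

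- Independent items, 0.74 × c⁴: 0.74 × 0.0625 = 4.6%; 0.74 × 0.4096 = 30.3%.
- Full overlap (the same women meet all four), 0.74 × c: 0.74 × 0.5 = 37%; 0.74 × 0.8 = 59.2%.

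If the timing condition is added as a fifth independent item at the same rates, the first pair falls to 0.74 × 0.5⁵ = 2.3% and 0.74 × 0.8⁵ = 24.2%. The full-overlap pair does not change.

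**4. What a 10-point attendance gain would look like.** Assumption: new attenders meet the items at the same rates, and the education does not otherwise change the items.

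- Independent: 10 × 0.0625 = 0.6 points; 10 × 0.4096 = 4.1 points.
- Full overlap: 10 × 0.5 = 5 points; 10 × 0.8 = 8 points.

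**5. Whether the sample sizes are affected.** In the precision formula p(1 − p) is largest at p = 0.5, where n = 1.31 × 1.96² × 0.25 / 0.05² = 503.2, or 504. No ANC prevalence can need more than that, and the survey uses 1,104. The proportions and intra-cluster correlation behind the trial's 1,126 are not given, so an effect on it cannot be checked.

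**The case against.** The best defence is that the paragraph is one cumulative definition: a visit, and in addition the timing, and in addition the content. The standardization argument concerns numbers of visits, so the EDHS comparison may attach only to the visit threshold, and the sponsor may have wanted a content-qualified measure. That is a legitimate choice of endpoint. It does not remove the conflict, because the opening sentence still counts any woman with one contact, the resulting measure is not EDHS-like, and the 74% does not appear to describe it.

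Several stronger conclusions are tempting, and the protocol does not support them:

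- *Sites would code the same woman differently.* No independent coding by site is described. One trained and supervised team uses a structured questionnaire, and recoding happens at analysis. The ambiguity is an analyst-level choice.
- *The sample size is wrong.* The 392 reproduces and is superseded by 1,104, and the inputs to 1,126 are not shown.
- *A planned comparison with the national figure fails.* The protocol speaks of comparison between studies in general and states no such analysis.
- *The laboratory items depend on facility supply, so real gains are hidden.* Nothing in the protocol documents availability of tests or tablets. Taking tablets is also maternal behaviour, and the sessions cover normal pregnancy and the benefits of using services. Education could raise iron-folic acid or tetanus uptake, so the all-or-nothing measure could move by more than step 4 shows.

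The low range of 5% to 30% also depends on independence. Items received at the same visits may well go together, which is why the full-overlap range belongs beside it.

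**Conclusion.** The contradiction holds on the text alone and needs no assumption: the ANC paragraph contains a contact rule and an all-or-nothing rule, and they classify attenders differently. A statistical analysis plan, if one exists, would have to override one of two rules that the protocol already states.

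The size is only indicative. With assumed item rates of 50% to 80%, the all-or-nothing prevalence runs from about 5% (independent items) to 59% (full overlap) against 74%, and a 10-point attendance gain would appear as about 0.6 to 8 points if the items are otherwise unchanged. A reader might infer that the trial is underpowered or that its effect will be biased in a known direction. The protocol supports neither. What is shown is an endpoint with two scorings, left open in an unblinded trial. It should be settled before outcome data are coded.

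**What to change.** 1. Under The measurements, make at least one ANC visit with a listed skilled provider the single ANC utilization outcome. This follows the opening sentence and the EDHS rationale already given.
2. Remove *must* from both the timing sentence and the iron-folic acid, tetanus, syphilis and blood-group sentence. Changing only the second would leave the woman first seen at 20 weeks in conflict.
3. Report timing and each content item as separate indicators, with a count of content items (0 to 4) among attenders.
4. Align Sample size calculation (say what the 74% measures), The study variables (give the scoring rule) and The measurements.

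If the sponsor does intend a composite, name it as one, give it a full scoring rule and its own planning proportion, and drop the statement that it resembles the EDHS measure.

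The cost is a reworded definition and short edits in two other sections. The same questions are asked and no new data are needed. The small downside is that the simpler outcome says less about quality of care, which the separate indicators still report.
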